### 11.8 Supportive Therapies

#### 11.8.1 Antidiarrheals

For symptoms of diarrhea and/or abdominal cramping that occur at any time during a treatment cycle with 5-FU, patients will be instructed to begin taking antidiarrheal medications at the physician discretion. Additional antidiarrheal measures may be used at the discretion of the treating physician. Patients should be instructed to increase fluid intake to help maintain fluid and electrolyte balance during episodes of diarrhea.

### **11.8.2 Hematopoietic Growth Factors**

Use of granulocyte colony-stimulating factor (G-CSF, filgrastim, Neupogen®) is permitted at investigator discretion. The use of erythropoietin and its analogues, such as darbepoetin, is also permitted at the discretion of the treating physician. ASCO guidelines for the use of colony-stimulating factors should be consulted.

### **11.8.3 Other Concomitant Medications**

Therapies considered necessary for the patient's well-being may be given at the discretion of the investigator. Other concomitant medications should be avoided except for analgesics, treatments for chronic medical conditions, or agents required for life-threatening medical problems. If possible, the use of drugs with laxative properties should be avoided because of the potential for exacerbation of diarrhea. Patients should be advised to contact the physician to discuss any laxative use. International normalized ratio (INR) elevations, bleeding, or both have been reported in some patients taking warfarin concurrently with 5-fluorouracil-containing chemotherapy. Patients taking warfarin should be monitored regularly for changes in prothrombin time (PT) or INR. Concomitant use of medications known to affect the conductive system, such as beta-blockers, calcium channel blockers, or digoxin, is allowed under investigator supervision.

## **12.0 CRITERIA FOR THERAPEUTIC RESPONSE/OUTCOME ASSESSMENT**

The primary objective of this study, 3-year DFS, will be assessed on the basis of surveillance procto/sigmoidoscopy, physical examination, and follow-up radiologic scans. For patients who receive TME or NOM, follow-up scans will occur according to current NCCN guidelines for rectal cancer surveillance. Patients in the NOM group will be evaluated using rectal MRI and endoscopic exam (section 10). Patients in the NOM group who undergo subsequent TME will be followed according to current NCCN guidelines. 3-year DFS will be defined as the percentage of patients alive without recurrence of disease at 3 years measured from the date of randomization. Patients in the NOM protocol who develop relapse at the site of the primary tumor but undergo curative TME with negative resection margins will not be counted as having recurrence. However, any patients developing local recurrence after TME, performed either immediately after neoadjuvant therapy or after a period of NOM, will be counted as having recurrence. Scans will be reviewed at MSKCC to resolve any discrepancies in interpretation. Scans showing equivocal evidence of local recurrence will be evaluated with additional imaging as necessary. Biopsy confirmation of local recurrence will be indicated for the purposes of the protocol. Isolated elevation of CEA, in the absence of other evidence of recurrent disease, will not be considered indicative of either local or systemic relapse. Symptomatic evidence of local recurrence will be corroborated on the basis of imaging and/or physical examination. Distant recurrence will also be assessed using follow-up CT scans of the chest, abdomen and pelvis. The MSKCC radiologist will review scans to resolve any discrepancies in interpretation. Central radiology review at MSKCC will review all incoming images and reports, but will only submit feedback on cases in which scans must be repeated or, in the case of interval or re-staging evaluations, where progression is identified in disagreement with the site investigator's assessment. Scans with equivocal evidence of distant recurrence will be evaluated via additional imaging, as

necessary. Biopsy confirmation of distant recurrence will be indicated for the purposes of the protocol.

Adverse events associated with CT and RT-CT will be assessed using the standard criteria described in section 11.0.

Surgical complications following TME will be assessed and recorded by the treating physician according to the Clavien-Dindo classification of surgical complications. [88] Refer to Appendix N to see the full scale.

### **13.0 CRITERIA FOR REMOVAL FROM STUDY**

All patients will be followed for five years from the last date of treatment. Only patients that choose to withdraw consent will be removed from the study and will no longer be followed.

A patient has the right to withdraw from the study at any time for any reason without prejudice to his/her future medical care by the physician or at the institution.

Every effort will be made to evaluate patients for eligibility prior to enrollment. However, if it is discovered that a patient is found to be ineligible after enrollment, the patient will be removed from the study.

Patients may discontinue protocol treatment without being taken off study. Patients who do not complete protocol treatment will remain on study but will be treated at the discretion of their treating physician. Patients placed on the NOM arm who then undergo TME at a later date will remain on study and be followed according to current NCCN guidelines.

If a patient chooses to discontinue treatment, is removed for clinical reasons, and/or received non-protocol treatment, the study team will continue to follow the patient based on intent-to-treat and collect data for up to five years.

Patients may discontinue treatment for any of the following reasons:

1. Unacceptable toxicity, both severe and unexpected
2. Investigator considers it would be in the patient's best interest to not continue
3. Patient is unwilling or unable to continue study treatment
4. Patient becomes pregnant
5. Lost to follow-up

Patients that discontinue protocol treatment must be followed for existing adverse events (AEs) for 30 calendar days after the last day of study treatment. All Grade  $\geq 3$  events considered unexpected and SAEs (as outlined in 17.2) occurring during that period must be reported to the participating site IRB and MSK per section 17.2. These events must be followed up until resolved, unless the condition is unlikely to resolve because of underlying disease, in the treating physician's opinion. After the 30-day period, patients will be followed for disease and survival status for up to 5 years. Limited information about subsequent treatment will be collected and may include chemotherapy, radiation therapy, and clinical exams, and imaging.

If a patient does not return for a scheduled visit, every effort should be made to contact him/her. In any such circumstance, every effort should be made to document the subject's outcome. Patients who leave MSKCC or the treating site or continue their care elsewhere will be contacted every 6 months by telephone, email, or mail. After three failed attempts to reach the patient, either via mail or telephone or a combination of the two, contact will cease and the patient will be considered lost to follow-up.

In the event of death while on study, death will be recorded as a Grade 5 SAE. If death is due to progression, this will be captured accordingly as death is a possible outcome.

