## **4.0 OVERVIEW OF STUDY DESIGN/INTERVENTION**

## 4.1 Design

This is a multicenter phase II study investigating the efficacy of TNT and selective NOM in patients with LARC. Patients with MRI-staged Stage II (uT3-4, uN-) or Stage III (any T, N+) rectal cancer and would be considered to require a complete TME at baseline will be randomized to receive FOLFOX/CapeOX before (Arm 1 or INCT) or after (Arm 2 or CNCT) 5-FU or capecitabine-based CRT. An interval evaluation will be conducted after completion of INCT in Arm 1, and after completion of CRT in Arm 2. Patients with tumors progression at the time of the interval evaluation will be treated according to standard practice per treating institution guidelines. Those with evidence of stable disease or tumor response will complete neoadjuvant therapy. Patients in both arms will be re-staged after completion of all neoadjuvant therapy. Patients with incomplete response will undergo a TME. Patients with complete or near complete clinical response will be treated with NOM. Criteria for determining complete, near complete and no incompleteresponse are outlined in Section 9.3.2. Patients in both groups (TME and NOM) will be followed according to NCCN guidelines. For study purposes, all patients will be followed for five years from the last date of treatment. For patients in the TME group, last date of treatment will be the date of surgery. For NOM patients, including those who undergo subsequent TME, last date of treatment is the last date of neoadjuvant treatment. Patients in the NOM group will be evaluated using rectal MRI and endoscopic exam (see section 10). Patients in the NOM group who undergo subsequent TME will be followed according to current NCCN guidelines. All patients will be followed based on intent-to-treat. Disease-free survival will be measured after three years.

The study is designed to test the hypothesis that patients with LARC treated with TNT and TME or NOM will have an improved 3-year DFS compared to patients with similar tumors treated with CRT, TME and ACT. We will measure QoL in patients treated with TNT and TME with patients treated with TNT alone. We will also compare INCT to CNCT with respect to organ preservation at 3 years, compliance with treatment, adverse events, and surgical complications.

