## 14.0 BIOSTATISTICS

**14.1 Primary objective:** *To evaluate 3-year DFS survival in patients managed with TNT and TME or NOM, compared with standard historical controls managed according to standard of care (CRT and TME followed by ACT).*

We hypothesize that 85% of patients with LARC treated with TNT and selective NOM will be alive and free of disease at 3 years. The 3-year DFS for similar patients (stage II/III LARC within 6 cm from the anal verge) treated according to the standard of care (CRT, TME, and ACT) is 75%. (Survival data provided by Maas et al from a pooled analysis of 3105 rectal cancer patients treated with CRT and TME). [35] In this trial, each arm is designed as a single-stage study that discriminates between 3-year DFS rates of 75% (historical control) and 85% (Study Arms, INCT and CNCT). No formal statistical comparison of the two arms is planned.

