For our power calculation, we assume uniform accrual over time and an exponential distribution for time to death. Based on our previous experience, we can assume that we will be able to accrue 2-4 patients per arm per month. Using the approach proposed by Lawless (1982), for 86% power, a two-sided type I error of 5% we will require 101 patients per arm. Based on our estimated accrual rate, a total of 202 patients can be accrued over 40 months with an additional 3-year follow-up.[95] With a sample size of 101 patients (each arm), we will consider the treatment regimen of an arm worthy of further study if the 3-year DFS rate exceeds (based on parametric exponential estimate) .82 (the upper critical value). The 3-year rates will be estimated using parametric exponential estimates as well as on Kaplan-Meier estimates. Analysis of the primary endpoint will occur 3 years following the completion of accrual. We anticipate about 10% loss to follow-up (dropouts that occur before the entire regimen has been completed), and will recruit an additional 10 patients per arm to account for this. Patient accrual for the entire trial is expected to take 40 months, with approximately 6 patients (2-4 per arm) per month. We will update the analysis after we have completed follow-up. Accrual has been completed a year ahead of schedule. Preliminary results indicate that we may require additional patients to detect differences in organ preservation rates, one of the secondary aims of this study. Based on this new information, we plan to increase accrual to 325 patients. As accrual has been progressing faster than initially estimated, we expect that, with the proposed increase, accrual will still be completed within the initially proposed accrual period.

This trial could complete with 3 possible results: both arms are worthy of further study, one arm is worthy of further study, no arm is worthy of further design. In all three cases, all Aim 2 analyses will be performed. In the ambiguous case when both the INCT and CNCT arms are worthy of further study, we will use a pick-the-winner strategy based on the number of NOM patients. This is described in more detail in section 14.2.

**14.2 Secondary objective 1.:** *To compare outcomes in patients treated on the two arms of this study, with respect to rates of organ preservation, compliance with the neoadjuvant protocol, and major adverse events.*

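### Section 13.0 contradicts itself on removing patients found ineligible after enrolment, and read literally it can bias 3-year DFS

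*Protocol*

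**What the plan says.** Protocol Section 13.0 opens with two general rules: "All patients will be followed for five years from the last date of treatment", and "Only patients that choose to withdraw consent will be removed from the study and will no longer be followed". Two paragraphs later it adds that "if it is discovered that a patient is found to be ineligible after enrollment, the patient will be removed from the study". That sentence gives no time limit and does not mention randomization.

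The same section then covers patients who stop treatment, are removed for clinical reasons or receive non-protocol treatment. For them "the study team will continue to follow the patient based on intent-to-treat and collect data for up to five years". Patients found ineligible are not named there.

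Section 4.1 states "All patients will be followed based on intent-to-treat", and the summary in Section 1.0 says the same. Section 12.0 anchors the primary endpoint at randomization: "3-year DFS will be defined as the percentage of patients alive without recurrence of disease at 3 years measured from the date of randomization". Section 14.1 judges each arm on its own against a cut-off of .82, set for 101 patients per arm. Planned accrual was later raised to 325 in total.

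**The concern.** A site that discovers after randomization that a patient was ineligible has two opposite instructions in one section: keep the patient, because consent was not withdrawn, or remove the patient. Sites may choose differently.

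The choice can affect the primary endpoint. The trial is not blinded (Section 15.2), and several entry criteria carry prognosis, for example absence of distant metastases (Section 6.1) and resectability of the primary (Section 6.2). A poor course can prompt a second look at the baseline staging. If patients with early failures are then removed and their outcomes are no longer collected, the arm's DFS is estimated in a favourably selected group and compared with a fixed threshold. Outcome data that were never collected cannot be recovered by an analysis plan.

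**Working it through.** **The texts side by side**

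- Sole ground for removal: withdrawal of consent (13.0, first paragraph).
- Second ground: ineligibility discovered after enrolment, at any time (13.0, third paragraph).
- Follow-up of all patients by intent-to-treat (1.0, 4.1), with DFS counted from randomization (12.0).

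The first two are logically incompatible. The second is compatible with the third only if it applies before randomization, and it is not so limited.

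**Reproducing the design figure**

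Section 14.1 states "for 86% power, a two-sided type I error of 5% we will require 101 patients per arm", for DFS of 75% against 85%, uniform accrual over 40 months, 36 months of further follow-up and exponential times.

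- Hazards per year: −ln(.75)/3 = 0.0959 and −ln(.85)/3 = 0.0542.
- Event probability: 1 − [exp(−3λ) − exp(−6.333λ)]/(3.333λ). Times 101, this gives 36.2 expected events under 75% and 22.5 under 85%.
- Survival scale, under 75%: SE = 0.2877 × .75/√36.2 = 0.0359, so the critical value is .75 + 1.96 × 0.0359 = .820.
- Survival scale, under 85%: SE = 0.1625 × .85/√22.5 = 0.0291, so power is about 0.846. The cube-root-hazard scale gives 0.867 with critical value .816.

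The stated 86% and .82 are reproduced, so the sample size is not in dispute.

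**Direction and size of the bias in DFS**

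Let S be DFS in all randomized patients, f the share removed and q the DFS of those removed. The DFS left for analysis is (S − f·q)/(1 − f). The protocol gives neither f nor q, so both are assumptions. With S = .75:

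| f | q = 0 | q = 0.5 | q = 0.75 | q = 0.9 |
|---|---|---|---|---|
| 1% | .758 | .753 | .750 | .749 |
| 3% | .773 | .758 | .750 | .745 |
| 5% | .789 | .763 | .750 | .742 |

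The estimate rises if the removed patients do worse than the rest, falls if they do better, and is unchanged if they do the same.

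**Chance of passing .82 when true DFS is 75%**

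This was simulated under the design assumptions, dropping the k earliest events in every trial. It is a worst case: every removed patient is a failure, and the earliest one. The values of k are assumptions. The .82 cut-off is kept at the larger sizes because the protocol states no other; 325/2 is about 162 per arm.

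| Patients per arm | None removed | k = 3 | k = 5 |
|---|---|---|---|
| 101 (design) | 2.1% | about 6.9% | 13.0% |
| 111 (with dropout allowance) | 1.7% | about 5.5% | about 10.3% |
| about 162 (current plan) | 0.5% | 1.6% | about 3% |

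Simulation error moves these by a few tenths of a point.

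A hand check of the mean estimate: at 101 per arm, losing 5 of 36.2 expected events cuts the hazard by 13.8%, and .75^0.862 = .780, against a simulated .779. At 162 per arm, expected events are 36.2 × 162/101 = 58.1. Losing 5 cuts the hazard by 8.6%, and .75^0.914 = .769.

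Censoring these patients at removal instead of deleting them gives nearly the same answer (13.4% at 101 per arm, k = 5). Removing patients at random leaves the mean at .750 and the chance of passing at 2.1% to 2.5% for 101 per arm.

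**The case against.** Several points limit the concern, and most of them stand.

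- **End of follow-up is an inference.** Section 13.0 attaches the end of follow-up only to withdrawal of consent. The same section keeps following patients removed for clinical reasons, so removal there does not always end follow-up. No text says ineligible patients leave the DFS analysis, and the analysis population may be defined in an SAP not at hand. A reader might infer that their outcomes are certainly lost; the document does not support that. What remains is that an unqualified instruction to remove a patient from the study is naturally read that way by a site.
- **There is a harmless window.** Section 15.1.1 confirms enrolment while the eligibility checklist may still be incomplete, and Section 15.2 delays randomization of such patients until the documents are complete. Removal in that window does not breach intent-to-treat, and it may be what the sentence was written for. The number of randomized patients exposed is probably small, but the sentence is not confined to this window.
- **Prognosis is not known to drive removal.** Eligibility describes status at entry, so a metastasis that develops later is an event, not ineligibility. Nothing in the protocol shows that ineligibility is found mainly in patients who do badly. Over-staged or otherwise good-risk patients could be removed too, which would lower DFS.
- **The comparison between arms.** A reader might infer that the randomized DFS comparison is compromised. Section 14.1 plans no formal comparison of the arms. Only the secondary comparisons and the selection rule in Section 14.2 could be touched, and that effect was not quantified.

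**Conclusion.** The contradiction within Section 13.0 is literal and needs to be resolved. The conflict with intent-to-treat follow-up holds for any patient removed after randomization. The effect on 3-year DFS is a possibility, not a demonstrated bias: it requires removal to be related to prognosis, and its direction is not fixed.

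The 13.0% at 101 per arm should not be read as the expected inflation. It combines an assumed five removals, worst-case selection and a sample size since enlarged. The worst case relevant to the current plan is a rise from about 0.5% to 1.6% with three removals or about 3% with five, if the cut-off stays at .82. The effect is therefore modest under the present sample size. It is still worth correcting, because outcome data not collected cannot be regained later.

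**What to change.** Reconcile the two sentences in Section 13.0. Limit removal for ineligibility to patients not yet randomized. State that every randomized patient, including one later found ineligible, stays in follow-up and in the primary DFS analysis by assigned arm unless consent is withdrawn. Simply deleting the sentence would leave no rule for ineligibility discovered late, so a replacement is better.

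Add an eligible-only sensitivity analysis, with ineligibility based on status before randomization and judged without knowledge of outcome. Keeping a patient in follow-up prescribes no treatment.

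The cost is a short amendment and continued follow-up of a few patients. The downside is that the primary estimate will include a few patients outside the target population, which the sensitivity analysis addresses.

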## 14.0 BIOSTATISTICS

**14.1 Primary objective:** *To evaluate 3-year DFS survival in patients managed with TNT and TME or NOM, compared with standard historical controls managed according to standard of care (CRT and TME followed by ACT).*

We hypothesize that 85% of patients with LARC treated with TNT and selective NOM will be alive and free of disease at 3 years. The 3-year DFS for similar patients (stage II/III LARC within 6 cm from the anal verge) treated according to the standard of care (CRT, TME, and ACT) is 75%. (Survival data provided by Maas et al from a pooled analysis of 3105 rectal cancer patients treated with CRT and TME). [35] In this trial, each arm is designed as a single-stage study that discriminates between 3-year DFS rates of 75% (historical control) and 85% (Study Arms, INCT and CNCT). No formal statistical comparison of the two arms is planned.

For our power calculation, we assume uniform accrual over time and an exponential distribution for time to death. Based on our previous experience, we can assume that we will be able to accrue 2-4 patients per arm per month. Using the approach proposed by Lawless (1982), for 86% power, a two-sided type I error of 5% we will require 101 patients per arm. Based on our estimated accrual rate, a total of 202 patients can be accrued over 40 months with an additional 3-year follow-up.[95] With a sample size of 101 patients (each arm), we will consider the treatment regimen of an arm worthy of further study if the 3-year DFS rate exceeds (based on parametric exponential estimate) .82 (the upper critical value). The 3-year rates will be estimated using parametric exponential estimates as well as on Kaplan-Meier estimates. Analysis of the primary endpoint will occur 3 years following the completion of accrual. We anticipate about 10% loss to follow-up (dropouts that occur before the entire regimen has been completed), and will recruit an additional 10 patients per arm to account for this. Patient accrual for the entire trial is expected to take 40 months, with approximately 6 patients (2-4 per arm) per month. We will update the analysis after we have completed follow-up. Accrual has been completed a year ahead of schedule. Preliminary results indicate that we may require additional patients to detect differences in organ preservation rates, one of the secondary aims of this study. Based on this new information, we plan to increase accrual to 325 patients. As accrual has been progressing faster than initially estimated, we expect that, with the proposed increase, accrual will still be completed within the initially proposed accrual period.

This trial could complete with 3 possible results: both arms are worthy of further study, one arm is worthy of further study, no arm is worthy of further design. In all three cases, all Aim 2 analyses will be performed. In the ambiguous case when both the INCT and CNCT arms are worthy of further study, we will use a pick-the-winner strategy based on the number of NOM patients. This is described in more detail in section 14.2.

**14.2 Secondary objective 1.:** *To compare outcomes in patients treated on the two arms of this study, with respect to rates of organ preservation, compliance with the neoadjuvant protocol, and major adverse events.*

Based on previous data, we anticipate a 20% NOM in the INCT arm, and 35% in the CNCT arm, after 3 years. The proportion of patients initially entered in the NOM protocol will be higher, but some will later relapse and require TME. For this reason, we anticipate that the proportion of patients with NOM at 3 years will be close to the pCR rates observed in previous studies. We estimated that the 222 patients required for the primary aim would be sufficient to detect differences in organ preservation rates. Our preliminary results indicate that the proportions of patients selected for NOM based on tumor response after completion of neoadjuvant therapy are much greater than expected: 66% in one arm and 79% in the other. Although many of these patients may eventually experience tumor regrowth requiring total mesorectal excision, the proportions of patients with a preserved rectum 3 years after diagnosis are likely to be greater than the original estimates. Therefore, based on the new information, we plan to increase accrual to 325 patients. There is limited information regarding treatment compliance and adverse events in patients who have received more than 4 or 6 cycles of INCT or CTNT. Therefore, these secondary objectives are considered exploratory. If both arms meet the endpoint in primary objective, we plan to use NOM rate to determine the more promising regimen using a “pick the winner” strategy. We will calculate the number of patients treated with NOM who are alive and free of disease 3 years following the start of the study. We will require at least 20 NOM patients in each arm to employ the following strategy: If there is a difference of 5 NOM patients between arms, the arm with more NOM patients will be deemed the winner. With 101 patients in each arm, 20% NOM in patients treated with INCT and 30% in patients treated with CNCT, we will have an 83% probability of selecting CNCT, a 1% probability of selecting INCT, and a 16% probability of considering the study inconclusive.

In addition, we will calculate therapy compliance using the following measures: the number of days RT was held, the number of RT delays of  $\geq 1$  week, the number of dose delays and the number of dose reductions in INCT and CNCT. We will also calculate the rate of select hematologic events (as outlined in 17.2), select non-hematologic events (as outlined in 16.0), and unexpected Grade 3 or higher non-hematologic adverse events and surgical complications in each treatment arm. Comparisons will be done using the Wilcoxon Rank Sum test or the Fisher’s Exact test.

**14.3 Secondary objective 2.:** *To measure patient-reported functional outcomes and QoL in patients with LARC treated with NCT, CRT and NOM, and compare these to patients treated with TME.*

The primary analyses for this aim will use data combined across both treatment arms; however, differences according to treatment will also be investigated. The primary endpoint will be QoL as measured one year from the end of TNT. Secondary endpoints will be bowel, sexual, and bladder function. While the subscales will be reported, the primary secondary endpoints will be the total scores on the BFI, FSFI and IIEF. With a total of 325 patients accrued, we expect that 129 patients will obtain complete clinical response and 196 will undergo TME. Approximately 15 to 30 patients initially treated with NOM are expected to cross over to TME at some point during follow-up. For the primary analyses, the NOM group will include these cross-overs on an intent-to-treat analysis. In secondary analysis, patients who eventually crossed over to receive surgery will be included in the TME group. We define this analysis as a comparison between TME vs. durable NOM. Durable NOM is defined as 3-year disease-free survival. We expect that 70% of patients will complete the QoL assessment at 1 year. This response rate takes into account refusals to complete the QoL

questionnaires, and the approximately 20% of patients who will develop distant disease or die before the 1-year time point. Thus, at 1 year we expect to have information on 94 TME patients and 62 NOM patients.

The primary endpoint of QoL will be assessed using the EQ-5D index, an overall measure of QoL and health ranging from 0 (worst health) to 1 (best health). Comparison will be done using the two-sample t-test. The minimally important difference (MID) for 534 cancer patients in the United States has been estimated to be in the range of .05 to .09 when using ECOG performance status as an anchor (Pickard, Neary, Cella 2007). The standard deviation of the EQ-index was .15 in this patient population. With our sample size of 156, we will be able to detect a difference of .07 with 80% power and type I error of 5%, assuming a standard deviation of .15.

In secondary analyses we will use a t-test to compare the EQ-5D index, measured at 1 year, in patients with durable NOM vs. TME. The differences in EQ-5D index from 1 year to 3 years will also be compared in patients with durable NOM vs TME, using an ANCOVA model that adjusts for variables found to be significantly different by NOM vs TME. Trends in the EQ-5D from baseline, 12, 24, and 36 months will be graphed, and evaluated descriptively.

Similar analyses will be done to study all other patient-reported functional and QoL endpoint.

